#### Handling of missing data

3.9.4

Missing data will be addressed using multiple imputation by chained equations (MICE). We will generate *m* = 50 imputed datasets, including the intervention group, primary outcome, and all pre-specified covariates in the imputation model. Pooled estimates will be obtained using Rubin’s rules. Missing POD assessments are assumed to be missing at random. Longitudinal time-point information will be included in the imputation model. Complete-case analysis will be conducted as sensitivity analysis to verify the robustness of primary results.

#### Statistical significance and software

3.9.5

A two-sided *p*-value <0.05 will be considered significant for the primary outcome. The false discovery rate (FDR) for secondary outcomes will be controlled using the Benjamini-Hochberg procedure. Analyses will be performed using SPSS 26.0 and R 4.3.2.

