#### Interim analysis and stopping guidelines

3.9.6

We have planned a single pre-specified interim analysis to evaluate both efficacy and safety, to potentially stop the trial early for overwhelming benefit, futility, or safety concerns. The details are as follows:

(1) Timing: The interim analysis will be performed after 50% of the target enrollment (approximately 87 patients) have been recruited and have completed the primary outcome assessment (i.e., POD assessment on postoperative days 1–3).(2) Execution: The analysis will be conducted by the independent Data Safety and Monitoring Board (DSMB). The research team (including investigators and statisticians) will remain blinded until the DSMB communicates its recommendations. All unblinded interim statistical calculations are performed by an independent external statistician, and only summarized results are submitted to DSMB without disclosing group information to the research team.(3) Statistical boundaries: The O’Brien-Fleming spending function will be used to control the overall two-sided type I error rate at *α* = 0.05. This pre-specified sequential design results in a conservative boundary for the first interim look, requiring stronger evidence for early stopping.

(a) Efficacy boundary (*α*₁): The nominal two-sided significance level for the interim analysis at 50% information is *α*_1_ = 0.003. If the between-group comparison of the primary outcome (cumulative incidence of POD) yields a two-sided *p*-value <0.003, and the safety profile is acceptable, the DSMB may recommend early termination for overwhelming efficacy.(b) Futility boundary: A non-binding futility boundary will also be evaluated. If the conditional power to achieve a statistically significant result (*p* < 0.05) at the final analysis, given the observed data at interim, is calculated to be less than 10%, the DSMB may recommend early termination for futility. This indicates a very low probability that completing the trial would demonstrate the hypothesized treatment effect.

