##### Independent unblinded interim analysis

3.10.2.5

To assess safety and efficacy in a timely manner, an interim analysis will be performed when enrollment reaches 50% of the total sample size (approximately 87 participants), conducted by an independent unblinded statistician.

(1) Statistician qualifications: An independent statistician with no conflict of interest with the study team and with experience in clinical trial statistics will be appointed. This statistician will not participate in any clinical procedures or data collection and will be responsible solely for the design and execution of the interim analysis.(2) Analysis content: The analysis will focus on comparing adverse event rates (including mild and serious AEs) and SGB-related complication rates between groups, while also providing a preliminary analysis of the primary outcome (cumulative incidence of POD on postoperative days 1–3) to assess safety and efficacy trends.(3) Unblinding requirements: The independent unblinded statistician will have access to complete unblinded data (including group allocation, adverse event data, and outcome data) and will use prespecified statistical methods (chi-square test, logistic regression, etc.) to conduct the analysis, producing an interim analysis report for the DSMB.(4) Blind maintenance: During the interim analysis, the independent unblinded statistician will strictly maintain confidentiality, submitting the analysis report only to the DSMB. The study team (all researchers except the SGB operators) will remain blinded throughout, not accessing interim analysis results to avoid compromising objectivity.(5) DSMB decision-making: The DSMB will review the interim analysis report, focusing primarily on safety. If unacceptable risks are identified, the DSMB may recommend termination. If safety is satisfactory, the DSMB may recommend continuation or, based on interim results, recommend sample size adjustment.

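### The final test is left at p<0.05 after 0.003 is used at the interim, and a sample-size change on unblinded results is allowed with an ordinary final test, so the claimed 5% type I error is slightly exceeded and not assured

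*Protocol article*

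**What the plan says.** Section 3.9.6 (Interim analysis and stopping guidelines) plans one interim analysis at about 87 of 174 participants. It states that an O'Brien-Fleming "spending function will be used to control the overall two-sided type I error rate at" 0.05. It sets the interim efficacy level: "The nominal two-sided significance level for the interim analysis at 50% information is" 0.003. It prints no corresponding final level.

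Two places do state a level for the final analysis, and both use 0.05. Section 3.9.5 (Statistical significance and software) says a two-sided p "<0.05 will be considered significant for the primary outcome". The futility rule in 3.9.6 defines conditional power as the chance of a significant result (p "< 0.05) at the final analysis, given the observed data at interim").

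Section 3.10.2.5 (Independent unblinded interim analysis) gives the independent statistician full unblinded data, outcomes included, and has the report to the DSMB cover the primary outcome. It then says that, if safety is satisfactory, "the DSMB may recommend continuation or, based on interim results, recommend sample size adjustment". Section 3.9.2 names the ordinary chi-square as the primary test.

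**The concern.** There are two linked problems.

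- **Final threshold.** If 0.003 is used at the interim and the full 0.05 again at the end, the overall error must exceed 0.05. The level in 3.9.5 and the control claimed in 3.9.6 cannot both hold. A final p of 0.0495 would be significant under 3.9.5 and not significant under the boundary that 3.9.6 implies.
- **Sample-size change.** A change in sample size that depends on the observed treatment difference alters the null distribution of the ordinary pooled test. The protocol gives no rule, no cap and no adjusted statistic, and 3.9.6 does not list re-estimation among the purposes of the interim. The 5% control is therefore claimed for a design that is not fully fixed.

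At stake is the decision rule for the only primary outcome. Section 3.1.1 says nobody had been enrolled at submission, so it can still be settled before data exist.

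**Working it through.** **Inputs from the protocol.** Interim two-sided level 0.003 at information fraction t = 0.5; final level 0.05; overall target 0.05 (3.9.5, 3.9.6). Rates 40% and 20%, 78 per group before dropout, 87 per group after (3.8). The futility rule is non-binding, so it gives no type I error back.

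**Step 1: the interim level.** Lan-DeMets O'Brien-Fleming spending with 0.025 per side: 2[1 − Φ(z₀.₀₁₂₅/√t)] = 2[1 − Φ(2.241/0.707)] = 0.001525 per side, or 0.00305 two-sided. The stated 0.003 reproduces.

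**Step 2: overall type I error as written.** Under the null, Z₁ (interim) and Z₂ (final) are bivariate normal with correlation √0.5 = 0.707. The critical values are c₁ = 2.968 (p = 0.003) and c₂ = 1.960 (p = 0.05).

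Overall α = 1 − P(|Z₁| < c₁ and |Z₂| < c₂) = 0.0510.

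At information fraction 0.4 it is 0.0514; at 0.6 it is 0.0506.

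**Step 3: the matching final level.** Solving the same expression for an overall 0.0500 gives |Z₂| ≥ 1.968, that is p < 0.0490.

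**Step 4: power cost.** The drift at 78 per group is 0.20/√[(0.24 + 0.16)/78] = 2.793. Power with 0.003 then 0.05 is 79.8%; with 0.003 then 0.049 it is 79.6%. At 87 per group the figures are 84.0% and 83.8%.

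**Step 5: adding the sample-size change.** The protocol gives no rule, so these rules are assumptions. Each keeps 0.003 at the interim and the ordinary pooled test at 0.05 at the end. Stage 2 may grow up to 2-fold or 3-fold, which takes total N to 1.5 or 2 times plan. The null conditional error is integrated over Z₁. The first three rows raise N towards 80% conditional power under the observed trend.

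| Assumed rule | Type I error, 2-fold cap | 3-fold cap |
|---|---|---|
| N raised only if conditional power is at least 36% | 5.00% | 4.97% |
| N raised only if conditional power is at least 10% (the futility line) | 5.2% | 5.2% |
| N raised at any conditional power | 5.8% | 6.2% |
| Worst case: stage 2 size chosen to maximise the error | 5.9% | 6.3% |

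Lowering the final level to 0.049 while keeping the ordinary test leaves the worst case at 5.8% and 6.2%. Correcting the threshold alone therefore does not settle the second problem.

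**The case against.** The strongest defence is that naming the spending function and the look time already fixes the final level near 0.049. On that view 3.9.5 states only the overall level, and the boundary table belongs in a statistical analysis plan. This would answer a protocol that merely omitted the final level. It does not answer one that prints 0.05 as the significance level for the primary outcome and repeats it for the final analysis in the conditional-power rule.

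The defence is right about size. An excess of 0.1 point is smaller than the chi-square test's own discreteness: at 87 per group without an interim, a 0.05 cut-off has true size 4.94%, 5.12% and 5.30% at common rates of 20%, 30% and 40%.

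On the sample-size clause, a reader might infer that any unblinded change invalidates the chi-square altogether. The documents do not support that: the inflation depends on the rule, and the first row of the table shows a rule with essentially none. A reader might also quote 9% to 10% as the possible error. That requires stage 2 to range from about 2% of plan to 10 times plan, which nothing in the protocol suggests.

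It is also fair that the clause is a single permission in a paragraph centred on safety, and that 3.10.2.3 denies the DSMB primary-outcome efficacy statistics before the final analysis. That statement conflicts with 3.9.6, 3.10.2.4 and 3.10.2.5, so it leaves the position unclear and does not remove the problem. Section 3.8 calls the results hypothesis-generating, which softens the consequence but does not withdraw the claim of error control.

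**Conclusion.** The point holds, with a modest numerical effect. As written, 0.003 followed by 0.05 gives 5.10% overall. This rests on the normal approximation and an interim at half the information, and moves only between 5.06% and 5.14% for fractions of 0.6 to 0.4. The final level that agrees with 3.9.6 is 0.049.

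The sample-size clause is the weightier part. With it in place, 5% control is not assured. How far it fails cannot be stated from the protocol: between about 5.0% and 6.3% under the assumed rules, with stage 2 growing by at most two- to three-fold. The defect is a claim of control over a design left open, and no particular inflation is established.

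**What to change.** - **Sections 3.9.5 and 3.9.6:** state that the final analysis of the primary outcome is significant at two-sided p<0.049, recomputed from the spending function at the information fraction actually reached. Use the same level in the conditional-power rule.
- **Section 3.10.2.5:** delete the sample-size adjustment clause, or restrict it to blinded re-estimation from the pooled POD rate. If unblinded re-estimation is wanted, fix in advance the rule, a cap, and a weighted (Cui-Hung-Wang) or conditional-error (Müller-Schäfer) final test.
- **Section 3.10.2.3:** reconcile the DSMB's access to efficacy results with 3.9.6, 3.10.2.4 and 3.10.2.5.

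The cost is a few sentences and about 0.2 percentage points of power. The sample size of 174 need not change.

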#### Interim analysis and stopping guidelines

3.9.6

We have planned a single pre-specified interim analysis to evaluate both efficacy and safety, to potentially stop the trial early for overwhelming benefit, futility, or safety concerns. The details are as follows:

(1) Timing: The interim analysis will be performed after 50% of the target enrollment (approximately 87 patients) have been recruited and have completed the primary outcome assessment (i.e., POD assessment on postoperative days 1–3).(2) Execution: The analysis will be conducted by the independent Data Safety and Monitoring Board (DSMB). The research team (including investigators and statisticians) will remain blinded until the DSMB communicates its recommendations. All unblinded interim statistical calculations are performed by an independent external statistician, and only summarized results are submitted to DSMB without disclosing group information to the research team.(3) Statistical boundaries: The O’Brien-Fleming spending function will be used to control the overall two-sided type I error rate at *α* = 0.05. This pre-specified sequential design results in a conservative boundary for the first interim look, requiring stronger evidence for early stopping.

(a) Efficacy boundary (*α*₁): The nominal two-sided significance level for the interim analysis at 50% information is *α*_1_ = 0.003. If the between-group comparison of the primary outcome (cumulative incidence of POD) yields a two-sided *p*-value <0.003, and the safety profile is acceptable, the DSMB may recommend early termination for overwhelming efficacy.(b) Futility boundary: A non-binding futility boundary will also be evaluated. If the conditional power to achieve a statistically significant result (*p* < 0.05) at the final analysis, given the observed data at interim, is calculated to be less than 10%, the DSMB may recommend early termination for futility. This indicates a very low probability that completing the trial would demonstrate the hypothesized treatment effect.

### Data management and monitoring

3.10

#### Data collection

3.10.1

All study data will be collected and managed using the ResMan electronic data capture platform. Data entry will undergo double verification.

Participants will be assigned a unique study identifier (UID); all stored data will be pseudonymized. Access to the final dataset will be restricted to the principal investigator and statistician.

#### Safety monitoring and DSMB

3.10.2

##### DSMB composition

3.10.2.1

An independent Data Safety Monitoring Board (DSMB) has been established for this study, consisting of three external independent experts with no affiliation, academic collaboration, or financial relationship with the study team. One senior anesthesiologist from a provincial tertiary hospital, specializing in complication prevention for nerve blocks. One senior neurologist from a provincial tertiary hospital, responsible for assessing nerve injury-related adverse events. One biostatistician specializing in clinical epidemiology, responsible for interim data analysis and risk assessment. None of the DSMB members will participate in participant recruitment, clinical procedures, outcome assessment, or routine data management. All DSMB members will sign a Conflict of Interest Disclosure and a Confidentiality Agreement, committing to independent monitoring throughout the study, and will not disclose group allocation, participant data, or monitoring opinions until study completion and publication. The DSMB term is 2 years, renewable once. Any breach of confidentiality will result in immediate termination of DSMB membership and appropriate accountability.

##### Independence assurance

3.10.2.2

The DSMB is completely independent of the study implementation team and the sponsor, with independent authority to monitor, evaluate, and recommend study termination. The DSMB’s operational budget is managed independently without interference from the research group. The study team may attend DSMB meetings only to answer questions and may not participate in voting or influence safety decisions, ensuring objective and impartial monitoring.

##### Access to unblinded data

3.10.2.3

The DSMB will have access only to anonymized unblinded safety data, including participant group allocation, block procedure records, adverse event reports, and baseline medical history and medication data. The DSMB will not have access to personally identifiable information or to primary outcome efficacy statistics before the final analysis, balancing safety monitoring with blind maintenance.

##### Safety review frequency

3.10.2.4

A dual-mode review system will be implemented: routine scheduled reviews and emergency ad-hoc reviews.

(1) Routine reviews

(a) Initial review: After the first 10 participants have completed the SGB procedure and 24-h post-procedure monitoring, the DSMB will conduct an initial safety review, focusing on the safety of the SGB procedure, adverse event profiles, and feasibility of the monitoring protocol.(b) Regular reviews: After every 20 enrolled participants, the DSMB will conduct a regular safety review, summarizing adverse event data and procedure-related complications, assessing whether safety meets prespecified standards, and reviewing data integrity and completeness.(c) Interim review: When enrollment reaches 50% of the total sample size (approximately 87 participants), the DSMB will conduct an interim safety review, integrating results from the independent unblinded interim analysis to assess both safety and efficacy, and decide whether to continue, modify, or terminate the study.(d) Final review: After all participants have completed follow-up, the DSMB will conduct a final safety review, summarizing adverse event data across the entire study period, assessing overall safety, and issuing a final DSMB report.

(2) Emergency reviews

(a) If one SGB-related serious adverse event (e.g., LAST, pneumothorax, severe hematoma, nerve injury) occurs, the study coordinator will submit detailed information to the DSMB within 24 h. The DSMB will immediately initiate an emergency review to assess the association with the intervention and recommend whether to pause the study.(b) In cases of public health emergencies, major protocol amendments, or other urgent situations that may affect participant safety, the DSMB may independently initiate an emergency review.

(3) Review format

DSMB meetings will be conducted online or in person, with all members participating. The study coordinator will submit relevant data, and the principal investigator may attend only to answer questions (without voting rights). Written monitoring records will be signed by all DSMB members and archived.

##### Independent unblinded interim analysis

3.10.2.5

To assess safety and efficacy in a timely manner, an interim analysis will be performed when enrollment reaches 50% of the total sample size (approximately 87 participants), conducted by an independent unblinded statistician.

(1) Statistician qualifications: An independent statistician with no conflict of interest with the study team and with experience in clinical trial statistics will be appointed. This statistician will not participate in any clinical procedures or data collection and will be responsible solely for the design and execution of the interim analysis.(2) Analysis content: The analysis will focus on comparing adverse event rates (including mild and serious AEs) and SGB-related complication rates between groups, while also providing a preliminary analysis of the primary outcome (cumulative incidence of POD on postoperative days 1–3) to assess safety and efficacy trends.(3) Unblinding requirements: The independent unblinded statistician will have access to complete unblinded data (including group allocation, adverse event data, and outcome data) and will use prespecified statistical methods (chi-square test, logistic regression, etc.) to conduct the analysis, producing an interim analysis report for the DSMB.(4) Blind maintenance: During the interim analysis, the independent unblinded statistician will strictly maintain confidentiality, submitting the analysis report only to the DSMB. The study team (all researchers except the SGB operators) will remain blinded throughout, not accessing interim analysis results to avoid compromising objectivity.(5) DSMB decision-making: The DSMB will review the interim analysis report, focusing primarily on safety. If unacceptable risks are identified, the DSMB may recommend termination. If safety is satisfactory, the DSMB may recommend continuation or, based on interim results, recommend sample size adjustment.

##### Stopping rules for SGB-related adverse events

3.10.2.6

The study may be terminated if any of the following criteria are met:

Two or more SGB-related serious adverse events occur, including LAST, severe cervical hematoma, pneumothorax, persistent recurrent laryngeal nerve palsy, or intrathecal drug spread. The incidence of serious adverse events in the SGB group exceeds the pre-specified safety threshold of 5%, and the DSMB determines that this risk cannot be mitigated by modifying procedures or enhancing monitoring. The interim analysis shows a significantly higher total adverse event rate in the SGB group compared to the sham group (*p* < 0.05), and the difference is clinically meaningful, indicating unacceptable safety risks. A major safety hazard is identified in the SGB procedure that cannot be corrected through protocol amendments. Data fabrication or serious protocol violations occur that compromise data integrity and cannot be rectified.

If any of the above criteria are met, the DSMB will issue a written recommendation to suspend enrollment, modify the protocol, or terminate the trial. After the DSMB recommends termination, a written report will be submitted to the ethics committee and the Chinese Clinical Trial Registry. The study team will immediately stop participant recruitment and intervention, complete follow-up of enrolled participants to ensure their safety, and report to relevant authorities as required.

### Ethics and dissemination

3.11

The study protocol (Version 1.0, 2025.12.04) has been approved by the ethics committee of the Second Hospital & Clinical Medical School, Lanzhou University (Approval No. 2025A-1323). Written informed consent will be obtained from all participants. Important protocol modifications will be communicated to the ethics committee, trial registry, and investigators. Results will be disseminated through peer- reviewed scientific journals and conference presentations, regardless of outcome.

## Discussion

4

This protocol describes the design of a randomized controlled trial to evaluate the efficacy of a single preoperative SGB for preventing POD in gastrointestinal cancer surgery patients (16, 17). The study’s primary strength lies in its rigorous methodology— incorporating randomization, double-blinding with a credible sham procedure, standardized co-interventions, and validated outcome measures—which minimizes bias and enhances the validity of future findings.

The rationale for SGB is grounded in its potential to modulate two key POD pathways: neuroinflammation and autonomic dysregulation (17–21). It is important to emphasize that this rationale is primarily derived from studies on POCD, pain, inflammation, and other perioperative outcomes, rather than from direct evidence on POD (16, 17). Currently, direct clinical evidence for SGB preventing POD remains scarce, with existing human studies being small in scale or still at the protocol stage. Therefore, if our hypothesis is confirmed, SGB could represent a novel, targeted, and non-pharmacologic adjunct to existing delirium-prevention bundles. Its relatively short procedure time and favorable safety profile may facilitate clinical translation.

Several methodological limitations should be acknowledged. First, the single-center design may limit generalizability, though it ensures protocol consistency. Second, while we measure systemic inflammatory markers, direct assessment of central neuroinflammatory changes is not feasible in this clinical setting. Third, our sample size calculation assumed a 50% relative risk reduction, which may be optimistic in an elderly population (≥60 years) that already excludes cognitively impaired patients and additionally receives a standardized multicomponent delirium prevention bundle. Therefore, if the true effect is more modest, the study may be underpowered. The findings should be considered exploratory. Fourth, the biological rationale for SGB preventing POD is largely derived from indirect evidence (studies on POCD, pain, inflammation, and autonomic function). Direct evidence specifically targeting POD remains limited. Positive results would require replication in larger, independent cohorts. Fifth, all SGB procedures are performed on the right side, which limits generalizability to left-sided SGB. Sixth, maintaining blinding is challenging because Horner’s syndrome may be visible to participants and potentially to assessors. Although the performing anesthesiologist is unblinded by necessity and strict role separation (performer vs. assessor) mitigates this risk, we have incorporated a blinding effectiveness assessment (participant and assessor checks, see section 3.3). Results will be reported to allow readers to evaluate blinding success.

This trial will contribute high-level evidence regarding the role of neuromodulation in perioperative brain health. If SGB proves effective, future research could explore optimal dosing (volume/concentration), timing (pre- vs. post-operative), and its effects on long-term cognitive function.
